## Funding

This project was funded by the Programme Grants for Applied Research programme (RP-PG-1212-20015) and will be published in full in the NIHR Journals Library. This research presents independent research commissioned by the NIHR. The views and opinions expressed by authors in this publication are those of the authors and do not necessarily reflect those of the NHS, the NIHR, MRC, CCF, NETSCC, the Health Technology Assessment programme or the Department of Health.

### Role of study sponsor and funders

Neither the funder nor the sponsor have had any role in study design, data collection and analysis, decision to publish, or preparation of manuscripts.

## 1. Lay summary

Cystic Fibrosis (CF) is an inherited disease affecting 10000 people in the UK with an average age at death of 28 years in 2012. The lungs of people with CF (PWCF) are prone to infections. Daily physiotherapy and inhaled medications are needed to stay healthy. Around £30 million is spent annually on inhaled therapy but average adherence has been shown to be only 36%. Data suggest that adherence is better in younger children (71% in under 12s, falling to 50% in teenagers) but of the 10000 UK PWCF almost 6000 are now adults. PWCF who collect <50% of their medication cost the healthcare system significantly more than PWCF who collect more than 80% and most of the additional cost results from unscheduled emergency care and hospital admission. This unscheduled emergency care is distressing for PWCF and their families.

We have designed an intervention to help adult PWCF see how much treatment they use. We use dose-counting nebulisers to collect data and send it to a website where it can be displayed. We have worked with PWCF to make the information easy to understand. The website has modules which teach PWCF how to build successful treatment habits. We have developed a toolkit to help PWCF and a health professional (interventionist) work together to form habits of adherence to treatment.

The NHS should not fund this intervention without its effectiveness and value for money being evaluated in a Randomised Controlled Trial (RCT). However, there is currently insufficient information to effectively plan or justify funding a RCT on the scale required. This feasibility study is an essential preliminary to the full scale RCT. The purpose of this feasibility study is to see whether the proposed procedures for the full scale RCT are feasible and acceptable to PWCF. It will also tell us whether the intervention can be delivered by health professionals and is acceptable to PWCF, outside the NHS trust where it was developed.

We will recruit PWCF for four months at two CF units. We hope we will recruit 64 PWCF overall, but will deem the full scale RCT feasible if we recruit 48. A computer will decide whether people who consent to be in the study will receive usual care alone or also receive the intervention. Both groups have a short period of two to four weeks when data is collected through their nebulisers and fed back to the website. It is only after that period that those allocated to the intervention are allowed to use the website and receive enhanced care from the interventionist. After that point, all participants are followed up for 5 (+/-) months. Participants will complete a series of questionnaires at the outset and at 5 (+/-) months.

With appropriate consent, the interventionist or member of the multidisciplinary team (MDT) will audio record consultations between themselves and PWCF who are receiving the intervention or usual care. Qualitative researchers will conduct: 20-24 interviews with PWCF receiving the intervention; 20-24 interviews with PWCF receiving usual care; eight interviews with the four health professionals who are delivering the intervention; and eight semi-structured interviews with members of the wider MDT. These interviews are intended to help the team understand and mitigate potential sources of failure in the intervention and the proposed full-scale trial.

## 2. Introduction

### 2.1 Background

Cystic Fibrosis (CF) is a long term condition (LTC) in which poor adherence to high cost drugs shortens lives and increases NHS costs. CF is a LTC affecting 10,000 people in the UK with PWCF typically dying from lung damage at a median age of 28 years [1]. Randomised controlled trials show that preventative medications reduce exacerbations and/or preserve lung function, [2–8] however adherence is poor. A recent review of objective measures of adherence using medicine possession ratios (MPR: prescriptions collected over prescriptions issued) and instrumented medication monitors showed adherence ranging from 67% for oral antibiotics, 31-53% for inhaled antibiotics, 53-79% for mucolytics agents and 41-72% for hypertonic saline [9]. Accumulating evidence suggests poor adherence is associated with poor outcomes. PWCF collecting four or more courses of alternate month nebulised tobramycin per year were 60% less likely to be admitted to hospital than PWCF collecting one or less [10]. Lower composite MPR predicted exacerbations requiring intravenous antibiotics (IVAB) [9] and over a 12 month period PWCF with an MPR of 80% had significantly lower total healthcare costs than PWCF with an MPR <50% with a cost difference \$14,211 per patient and most excess costs related to hospital care [11]. Rescue therapy with IVAB can cause renal failure [12]. The total 2012 UK spend for CF was estimated to be £100 million of which £30 million was spent on inhaled antibiotics and mucolytics [13]. Although patient self-reported adherence to inhaled therapy was 80%, objective measurement showed median adherence was only 36% and the clinicians were unable to predict which PWCF were able to successfully adhere [14] making adherence support difficult. In 2012, the UK CF population received 171,907 days of IVAB with the 93,455 of these that occurred in hospital costing an estimated £27 million [15]. It is recommended that adherence interventions should be targeted where adherence really matters [16] and targeting support towards the high cost inhaled preventative drugs in CF (median adherence 36%) has the potential to impact on the 171,907 days of IVAB a proportion of which will represent rescue therapy necessitated by failed prevention.

### 2.2 Rationale

The National Institute for Health Research have commissioned a Programme Grant for Applied Research to systematically develop and evaluate an adherence intervention for PWCF. The Programme Grant has three work packages

Work package 1: Build IT infrastructure to capture adherence data from nebulisers. Co-produce a web-portal, 'CFHealthHub', with PWCF and clinicians, in order to display routinely collected adherence data for the use of both groups.

Work package 2: Develop a toolkit based on psychological theory that can support PWCF to adhere to treatment. This will include feedback of measured adherence data and personalised interventions to increase adherence delivered through CFHealthHub. Manualise a Behaviour Change Intervention (BCI) for use by health professionals and PWCF.

All four work packages have received a favourable opinion from an NHS REC:

- Work package 2.1A: A study of the views of people with cystic fibrosis about their condition and treatments (Hampshire A REC: 14/SC/1455; IRAS: 171049);

- Work package 2.1C: A study to produce videos for the CFHealthHub website (Camden & Kings Cross REC: 15/LO/0944; IRAS: 182367);
- Work package 2.2B: A study to develop a Behaviour Change Intervention (BCI) to help patients with CF manage treatment adherence ((South Yorkshire REC: 15/YH/0332; IRAS: 184477); and,
- Work package 2.2B(1): A study to understand how to use the eTrack and Bi-neb nebuliser to help people with CF to manage their inhalation treatments (West of Scotland REC 5: 15/WS/0089; IRAS: 177900).

Work package 3: Evaluate the toolkit developed in work package 2. The planned definitive evaluation will take place in a large-scale, multi-centre Randomised Controlled Trial (RCT). The definitive evaluation will compare usual care plus staff training in the importance of knowledge, skills and confidence building for adherence versus the same plus the structured behaviour change in intervention (CFHealthHub plus manual).

There is too little information available to effectively plan or justify funding a full scale RCT. We wish to conduct feasibility study comprising of:

- an ‘external pilot RCT’ to establish the feasibility of recruitment to a larger, definitive study; and,
- a ‘process evaluation’ which will help us understand the strengths and weaknesses of both the intervention and research protocols, and ways of addressing any weaknesses.

### 3. Aim and objectives

#### 3.1 Aims

The principal aims of this feasibility study are to assess the feasibility and acceptability of:

- a complex intervention, when delivered outside the team which conceived and developed it; and,
- procedures for a full-scale RCT.

#### 3.2 Objectives

1. An external pilot randomised controlled trial to determine feasibility of a randomised controlled trial based on objective stop-go criteria (Section 7.1) related to:

- (a) participant recruitment;
- (b) participant retention; and,
- (c) quality of primary outcome data at 5(+/- 1) month.

2. A process evaluation, relating quantitative and qualitative data on procedures to outcomes, in order to understand and mitigate potential sources of failure in:

- (a) the intervention; and,
- (b) the full trial.

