## 7. Outcomes

### 7.1 Feasibility outcomes ('stop-go' or 'success' criteria for RCT)

In line with proposed CONSORT extension for pilot studies [37], in this section, we state the criteria for success of the external pilot trial. The criteria are based on the primary feasibility objectives, which provide the basis for interpreting the results of the external pilot and for determining the feasibility of proceeding to the full-scale study scheduled for months 31 to 60 of the project. Depending on the funder's perspectives, the outcome of the external pilot might be:

- (i) "Stop - main study not feasible";
- (ii) "Continue, but modify protocol - feasible with modifications";
- (iii) "Continue without modifications, but monitor closely - feasible with close monitoring"; or,
- (iv) "Continue without modifications - feasible as is." [37]

We anticipate that modifications to the research protocol will be necessary as the feasibility study progresses. Some of the qualitative research will be undertaken early in the pilot trial and lessons learned about the trial procedures will be identified and acted on during the pilot trial. There are three objective stop-go criteria:

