#### **1. Feasibility of recruitment to RCT**

Defined as recruitment of no fewer than 48 participants randomised at two centres over four months, 75% of the rate required in the main trial;

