#### **2. Feasibility of retaining participants in the RCT**

Defined as attrition from the research protocol of no more than 15% of randomised participants at 5 (+/-1) months.

If these are met the full trial will go ahead. If these are not met overall, but are met in the last half of the pilot trial after trial procedures have been improved based on lessons learned from the early stage of the pilot trial, then the full trial will go ahead.

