### **7. Number of missing values/incomplete cases**

Assessed by data management team, based on data in Prospect database.

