#### **7.4.1 Primary clinical outcome**

The primary clinical outcome is the number of pulmonary exacerbations in 5 (+/-1) month post-baseline follow-up period, defined according to the Fuchs criteria [47]. An exacerbation of respiratory symptoms will be said to have occurred when a patient was treated with parenteral antibiotics for **any one of the following 12 signs or symptoms** [48]:

1. change in sputum;
2. new or increased hemoptysis;
3. increased cough;
4. increased dyspnea;
5. malaise, fatigue, or lethargy;

6. temperature above 38 °C;
7. anorexia or weight loss;
8. sinus pain or tenderness;
9. change in sinus discharge.
10. change in physical examination of the chest, derived from notes by site staff.
11. decrease in pulmonary function by 10 percent or more from a previously recorded value, derived from notes by site staff; or,
12. radiographic changes indicative of pulmonary infection, derived from notes by site staff.

The trial interventionist or prescribing clinician/nurse will collect data on the “exacerbations” form at the point of a participant starting a course of IV antibiotics.

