#### 7.4.2 Secondary clinical outcomes

##### 1. Body Mass Index (BMI).

2. **Forced expiratory volume in 1 second (FEV1):** standardised spirometry as a measure of condition severity [49].

3. **EuroQol EQ-5D-5L:** generic health status measure for health economic analysis [50].

4. **The Patient Activation Measure (PAM-13) (Health Style Assessment):** assessment of patient knowledge, skill, and confidence for self-management [51]. \*PAM-13 was labelled as “Health Style Assessment” following a request from the licence owners to ensure the purpose of the questionnaire is clear for participants.

5. **Assessment of routine :** measure of life chaos [52].

6. **Self-Report Behavioural Automaticity Index (SRBAI):** automaticity-specific subscale of the Self Report Habit index to capture habit-based behaviour patterns [53].

7. **Cystic Fibrosis Questionnaire-Revised (CFQ-R):** disease specific health-related quality of life instrument [54].

8. **The Patient Health Questionnaire depression scale (PHQ-8):** severity measure for depressive disorders [55].

9. **MAD (Medication Adherence Data-3 items) :** medication adherence measure

10. **The General Anxiety Disorder 7-item anxiety scale (GAD-7):** severity measure for anxiety [56].

11. **The Capability Opportunity Motivation Behaviour Beliefs Questionnaire (COM-BMQ):** This questionnaire incorporates:

- a. **The Beliefs about Medicines Questionnaire - specific (Nebuliser adherence) (BMQ 21-item):** a validated self-report tool[57], customised by the author to identify perceived necessities and concerns for nebuliser treatment.
- b. The following project-specific items: one additional belief item, one intention item, one confidence item, and a list of barriers. These will serve as a tailoring tool for the intervention and also as a secondary outcome measure.

12. **Subjective adherence single question:** self-report estimate of adherence as a percentage. Self-reported problems: identification of capability and opportunity barriers to nebuliser adherence

13. **Concomitant medications:** bespoke instrument, designed for this research project.
14. **Resource use form:** interventionist collects data from a combination of hospital notes and the NHS patient electronic system to determine 1) inpatient IV days 2) Routine clinic visits 3) Unscheduled outpatient contacts 3) unscheduled inpatient stays.

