### 10.1.3 Data quality assurance

Prospect provides a full electronic audit trail, as well as validation and verification features which will be used to monitor study data quality, in line with CTRU SOPs and the Data Management Plan (DMP). Error reports will be generated where data clarification is required. Rates of missing data and data points which are out of the expected or allowed range will be presented to the team at monthly management group meetings.

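### Objective 1(c) makes quality of primary outcome data a stop-go matter, but section 7.1 defines no criterion for it, and the stated data-quality measures cannot show an IV course that no exacerbations form recorded

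*Protocol*

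**What the plan says.** Section 3.2 lists recruitment, retention and "quality of primary outcome data at 5(+/- 1) month" as the matters on which feasibility will be decided, using objective criteria in section 7.1.

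Section 7.1 states "There are three objective stop-go criteria". Two follow: "recruitment of no fewer than 48 participants randomised at two centres over four months, 75% of the rate required in the main trial" and "attrition from the research protocol of no more than 15% of randomised participants at 5 (+/-1) months". The rule for going ahead comes straight after these two.

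Measures of data quality appear elsewhere:
- Section 7.2, item 7 (number of missing values or incomplete cases): "Assessed by data management team, based on data in Prospect database".
- Section 10.1.3: "Rates of missing data and data points which are out of the expected or allowed range will be presented" to the monthly management group.

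The primary clinical outcome (sections 7.4.1 and 11.1) is the number of IV-treated exacerbations per participant. It is recorded on a form "at the point of a participant starting a course of IV antibiotics". Table 3 also schedules that form at consent, at 5 months and up to 30 April 2017. A footnote to Table 3 requires the sign and symptom items only where the participant reports parenteral antibiotics.

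Section 7.4.2 provides two other views of IV treatment. For the resource-use form (item 14), the "interventionist collects data from a combination of hospital notes and the NHS patient electronic system to determine 1) inpatient IV days". Item 18 makes any IV antibiotic treatment an outcome in its own right.

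**The concern.** An outcome that counts events fails differently from a questionnaire score. An unreturned questionnaire leaves a blank that a missing-value count will find. An IV course that nobody records leaves no blank: the participant's count is one lower and the record looks complete. A missing-value or out-of-range rate is therefore the wrong instrument for the main way in which this outcome can go wrong.

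The point goes beyond the absent third criterion. If that gap were filled with a threshold on missing values, the threshold could be met however many courses had gone unrecorded.

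Two things are at stake. The pilot exists to test the procedures of the full trial, and it could pass the primary outcome on with its capture rate unknown. Section 11.1 also uses the estimated effect on exacerbations to confirm that the full trial is worth running. The study is open label, the interventionist both delivers the intervention and may complete the form, and the intervention arm has more interventionist contact. Capture could therefore differ between arms, although nothing in the protocol shows that it would.

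**Working it through.** **No stated figure is in dispute.** The pilot's own targets reproduce: 8 per centre per month × 4 months × 2 centres = 64, and 0.75 × 64 = 48.

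**Following a missed course through the protocol**
1. The form is not completed at IV start (section 7.4.1). No record exists, so nothing is blank.
2. The 5-month exacerbations form (Table 3) and the final visit (section 6.4.4.6) give a second chance. If the course is found in the notes or reported by the participant, it is recovered. If the whole 5-month form is absent, item 7 of section 7.2 can count it as missing.
3. If the 5-month form is completed but the course is neither reported nor found, the symptom items are legitimately blank under the Table 3 footnote. No missing value arises and the count is one too low.
4. The resource-use form may show inpatient IV days for that course, but no section compares it with the exacerbations forms.

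Step 3 cannot be seen by either stated measure. The recovery rate at step 2 is not reported either, although it would show how well capture at IV start works.

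**Scale (illustration)**

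Inputs: 171,907 IV days and 10,000 people (section 2.1); 5 months' follow-up; 14 days per course (assumed).
- IV days per person-year: 171,907 / 10,000 = 17.19.
- Courses per person in 5 months: 17.19 × (5/12) / 14 = 0.512.
- Expected courses: 0.512 × 64 = 32.7; 0.512 × 48 = 24.6; 0.512 × 32 = 16.4 per arm at the target size.
- If 20% escaped every route (assumed): 0.20 × 32.7 = 6.5 lost at 64 participants and 0.20 × 24.6 = 4.9 at 48. Missing values arising from these: 0.
- Sensitivity to course length, 64 participants: 45.8 courses at 10 days, 21.8 at 21 days.

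Poisson counts show why the loss is hard to see. With 80% capture, the share of participants with no recorded event, exp(−0.8 × mean) against exp(−mean), moves from 67% to 73% at a true mean of 0.4, from 45% to 53% at 0.8, and from 30% to 38% at 1.2. Each is a believable result.

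**Effect on the rate ratio (mechanism only)**

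Observed ratio = true ratio × (capture in intervention / capture in control). With assumed capture of 95% and 80%, 0.95 / 0.80 = 1.19, so a true 0.80 would read as 0.80 × 1.1875 = 0.95.

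**What the cross-check could deliver**
- Courses at home: section 2.1 puts 93,455 of the 171,907 IV days in hospital, so 78,452 / 171,907 = 46% were elsewhere. A check against inpatient IV days alone would not cover these.
- Precision (Wilson 95% intervals): 26 of 33 courses captured overall gives 79% (62% to 89%); 13 of 16 in one arm gives 81% (57% to 93%). The overall figure is useful; the by-arm figures are descriptive at best.

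**The case against.** The best defence is that capture does not depend on one event-triggered form. The form is scheduled again at 5 months in both arms, the final visit collects the primary outcome for everyone, section 5.1 names participant notes as the source, and section 6.6 continues collection from notes for those lost to follow-up. This stands. It narrows the problem to courses missed by every route, but it does not measure how many those are.

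Verification is also deferred to a Data Monitoring and Management Plan (section 10.1.1) and a Site Monitoring Plan (section 12.1), which are not shown and may include source checks. That is fair as to method. It does not answer section 3.2, which promises that the criterion itself is in section 7.1.

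Three stronger readings are tempting, and the protocol does not support them:
- A reader might infer that an unrecorded exacerbation is scored as zero. No such rule is stated. What follows from a count outcome is only that an unknown event cannot enter the count.
- A reader might infer that 1(c) will be judged by the missing-value count. Item 7 of section 7.2 is process data, and nothing assigns it to 1(c). The protocol assigns no measure at all.
- A reader might infer that the pilot will report near-complete data while losing a fifth of its events. The capture rates are assumptions, and the registry rate covers all ages rather than nebuliser users aged 16 and over.

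Finally, the same staff would read the same notes for both sources, so agreement may overstate capture. That is true of the remedy and belongs in the report.

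**Conclusion.** The point holds in a limited form. Section 3.2 makes primary outcome data quality a stop-go matter, section 7.1 omits the criterion, and neither stated data-quality measure can reveal an IV course missed both at its start and at 5 months. No section compares the exacerbations forms with the other IV information that the trial collects.

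The structural finding needs no numerical assumption. The size does: roughly 33 courses in 64 participants, or 25 in 48, rests on an all-ages registry rate and a 14-day course, and the losses and the shift from 0.80 to 0.95 rest on assumed capture rates. They show how the problem would act and do not predict that it will. The change should be made, because the pilot is the place to learn this capture rate and the sources are already being consulted.

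**What to change.** State the third criterion in section 7.1 as event capture, with the level judged acceptable fixed before the data are seen.

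- **Who:** every randomised participant, including those lost to follow-up whose notes may still be used.
- **Reference set:** all IV courses, inpatient and home, found at the 5-month point from the scheduled exacerbations form, the hospital notes, the electronic system already searched for the resource-use form, and the outcome on any IV antibiotic treatment. Use the same dates for every source. Section 7.4.1 asks for a form when an IV course starts, so all courses are the natural denominator.
- **Report:** the proportion of courses with a form completed at IV start, and the number found only by the cross-check; overall with a 95% CI, and descriptively by arm.
- **Keep** the missing-value and out-of-range rates as supporting information.

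Costs: one reconciliation and one table, with most of the work in tracing home courses, which the inpatient IV-days field does not hold. By-arm estimates will be imprecise at about 16 courses per arm under the assumptions above. Capture may be overstated where the same person reads the same notes, and the report should say so. The reported data quality may also look less favourable than a missing-value rate would.
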